#### 6c. Rapid ART initiation procedures (rapid initiation group)

The left side of Figure 1 illustrates rapid initiation procedures for the rapid group in Track 1.

##### *6c i. Rapid CD4 count and TB symptom screen*

The first step for rapid initiation will be a venous blood draw for a rapid CD4 count (and for other treatment initiation tests for those found eligible for treatment). For those offered rapid initiation, the blood sample will be processed immediately, on site, using the Pima Analyzer, rather than being stored for later transport to an off-site laboratory. The processing time for the Pima test is 20 minutes. In a validation study of Pima used at point of care clinics in South Africa, 7-9% of tests could not be read or had invalid results, due primarily to user errors in obtaining blood samples or filling cartridges. Careful training will be provided to study staff to minimize this type of error. A second Pima test will be run for subjects for whom the first Pima result is invalid. In addition, a blood sample will be sent to the off-site National Health Laboratory Service (NHLS) laboratory for all subjects in the rapid group for a confirmatory CD4 count. NHLS lab results will be monitored by the study team, and any subject found

not eligible for treatment using Pima but eligible based on lab results will be contacted by the study assistant and asked to return to the clinic to initiate treatment following rapid initiation procedures.

Patients who already have with them a valid CD4 count result (sample taken within the previous 6 months) will not have an additional CD4 count, though a blood sample will still be drawn for other required laboratory tests.

While awaiting CD4 test results, the study nurse will administer a TB symptom screen following South African guidelines for the definition of symptoms, for all subjects not already on TB treatment. Subjects with any TB symptoms will be asked to provide a sputum sample. The study nurse will also ask the subject about symptoms that might indicate a Stage 4/3 condition. Subjects who report such symptoms will be given a physical examination to determine if the condition exists and what treatment is needed.

Following the TB symptom screen and sputum collection and self-report of symptoms, patients will be asked to wait for a few minutes until their CD4 count is available, if it is not yet ready. Patients who have a CD4 count that makes them ineligible for treatment and do not have symptoms of TB or a Stage 4/3 condition will be informed of their CD4 count, thanked for their willingness to participate in the study, and asked to proceed with a standard pre-ART care visit. Those for whom a sputum sample has been sent for testing with Xpert will be asked to remain at the clinic until Xpert results are ready.

Patients eligible for treatment ( $CD4 \leq 350$  or TB or Stage 4/3 condition diagnosis) will also be informed of their CD4 count and asked to continue to the next step of the study.

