In Track 1, those in the rapid initiation group will be offered a rapid CD4 count, rapid TB test if needed, and other rapid tests and same-day physical exam, counseling, and adherence education on the same day as study enrollment, allowing immediate ART initiation if eligible. Those in the standard group will follow the standard-of-care visit schedule and procedures, which also include a CD4 count, TB test if needed, other tests, physical exam, counseling, and adherence education, though not on a rapid schedule. Subjects in Track 1 will be prospectively followed for a minimum of 10 months. Follow-up (after treatment initiation) will be passive and by medical record review only, to prevent biasing outcomes through active follow-up and maximize the extent to which study results reflect what could be expected in a routine implementation setting. An additional retrospective comparison group for Track 1 will be enrolled comprised of patients who became eligible for ART at one of the two study sites prior to the launch of the study.

Track 2 will be an observational evaluation only. Data from before the guideline change will be collected retrospectively, from existing registers and records at the site. Data from after the guideline change will be collected prospectively from questionnaires and newly-acrued medical record data. The study will not provide any direct clinical interventions for Track 2.

Unit cost data will be collected for all resources used for patient care for both study tracks, including all drugs, diagnostics, clinical staff time, and infrastructure and other fixed costs. Quantities of resources used will be collected from study case report forms at the end of the follow up period. An average cost per patient and cost per outcome will then be calculated and compared between the strategies.

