#### 8e. Medical record data

Most data for the study will be collected from the site's routinely maintained electronic medical records, which are maintained in an information system called Therapy Edge-HIV™. Records in this information system are typically only created once a patient starts ART. Paper-based medical records kept by the site will therefore be used to supplement the electronic medical record system as needed. The fields to be collected are listed below.

*To be used to link electronic and paper-based records to study identification number only:*

- Electronic medical record system number
- Clinic file numbers
- National ID number
- Name
- Date of birth

*All subjects at baseline (ART initiation):*

- Date of positive HIV test (if available)
- Sex
- Age in years
- Weight and height or BMI
- Date treatment eligibility determined, if reported
- Date and result of eligibility-determining CD4 count
- Date and result of TB symptom screen
- Date, type, and result of TB test(s)
- TB treatment, if relevant
- WHO stage and clinical conditions
- Date ART initiated (first dose of drugs dispensed)
- First-line regimen prescribed

*For all clinic visits for duration of study follow up, including initial visit and pre-ART visits (to be used to estimate resource utilization):*

- Date of visit
- Primary reason for visit (e.g. scheduled medical visit, medication pickup, unscheduled medical visit)
- Types of professionals seen (e.g. nurse, doctor, pharmacy assistant, counselor)
- Group and individual sessions attended (e.g. wellness course, adherence education)
- Numbers and types of all lab tests conducted (including CD4 counts and viral loads)
- Other procedures (e.g. x-rays) performed

- Medications prescribed and dispensed (ARV and non-ARV)
- Admissions for inpatient care since previous visit, if recorded
- Details of inpatient care received (facility, number of days, medications, lab tests, etc.) if recorded

*At interim and final dates of data censoring:*

- Date and result of most recent viral load test
- Status at clinic (in care / died / transferred to another site / stopped care / lost to follow up, defined as > 1 month late for last medication pickup)
- New or recurring HIV-related conditions
- Date and cause of death if applicable
- Date and result of most recent CD4 count

*Track 2 subjects only (pregnant women):*

- Gestational age at diagnosis or first ANC visit for current pregnancy if previously diagnosed
- Prior exposure to PMTCT

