#### 11c. Cost outcomes analysis

At the relevant endpoints (10 months after study enrollment for Track 1, delivery for Track 2, and other dates of data censoring), all resource usage and outcome indicators will be extracted from subjects' medical records and case report forms. Unit costs will be obtained from external suppliers and the site's finance and procurement records and applied to the resource usage data to provide a cost per study patient. Costs will be measured from the provider perspective and will include the cost of all resources utilized for each study subject, including drugs, laboratory tests, outpatient visits, and fixed costs such as building space, equipment, and management staff. We will estimate the average cost to the provider per patient achieving viral suppression by 10 months (Track 1) or adhering to ART until delivery as indicated by monthly medication pickup (Track 2). We will also estimate the average cost per other outcomes achieved, such as per patient remaining in care by specified endpoints. The average cost per outcome will then be compared between rapid and standard initiation groups to provide an estimate of the cost-effectiveness of the two strategies. Costs will be reported as means (standard deviations) and medians (IQRs) in rand and dollars.

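### As written, the cost analysis charges the rapid arm for a confirmatory off-site CD4 count that the strategy as described does not contain, a probably small bias against rapid initiation in a secondary outcome

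*Protocol*

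**What the plan says.** Section 5a describes the strategy: "those in the rapid initiation group will be offered a rapid CD4 count, rapid TB test if needed, and other rapid tests". It mentions no off-site confirmation. Section 6c i says the rapid group's sample is processed at once on site, "using the Pima Analyzer, rather than being stored for later transport to an off-site laboratory". The same section then has a further sample "sent to the off-site National Health Laboratory Service (NHLS) laboratory for all subjects in the rapid group for a confirmatory CD4 count", with one exemption: "Patients who already have with them a valid CD4 count result (sample taken within the previous 6 months) will not have an additional CD4 count". The study team watches the NHLS results, and any subject found "not eligible for treatment using Pima but eligible based on lab results will be contacted by the study assistant" is asked back to start treatment under the rapid procedures.

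Section 6d i describes a single off-site CD4 count for the standard group and no second one.

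For costs, section 8e lists the fields from which resource use is estimated, among them "Numbers and types of all lab tests conducted (including CD4 counts and viral loads". Section 11c takes the provider's perspective and says that costs "will include the cost of all resources utilized for each study subject, including drugs, laboratory tests, outpatient visits", together with fixed costs. Neither section separates a confirmatory test from the tests that make up the strategy. The resulting average cost per outcome is compared between rapid and standard initiation.

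**The concern.** Cost-effectiveness against standard care is one of the questions posed in section 3c, a secondary objective (4b) and a secondary outcome (11a ii). A clinic adopting the strategy as section 5a describes it would buy the point-of-care count and give up the off-site one. Under the costing rule as written, the rapid arm pays for both and the standard arm for one.

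This has a specific consequence. Any saving from no longer sending a sample off site cannot appear in the comparison, because the NHLS charge is carried by both arms. The error always runs in the same direction, so a larger sample does not reduce it. What is at stake is the rapid-arm cost per patient and per success, and the between-arm cost difference. The primary clinical outcome and the sample size are not affected.

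**Working it through.** The protocol states no unit cost and no expected cost difference, so there is no figure of its own to reproduce. The check counts the CD4 tests charged in each arm.

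**Inputs**
- Rapid group, no valid prior count: one Pima test and one NHLS test (6c i). With a valid prior count: no additional count, read here as covering both tests.
- Standard group: one NHLS count (6d i).
- Planned Track 1 prospective enrolment: up to 400, randomised 1:1, so about 200 rapid subjects (section 10).
- Planned success in the rapid group: 70% (section 10).
- Not given: NHLS unit cost c, Pima unit cost p, and the share s of rapid subjects without a valid prior count. I assume s between 25% and 100%. It may well be below 100%, because patients returning for a CD4 result are a named recruitment route (6b i).

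**Step 1: CD4 cost for one subject without a prior count (first Pima reading valid)**

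| Costing | Rapid | Standard | Rapid minus standard |
|---|---|---|---|
| As written | p + c | c | p |
| Without the confirmatory test | p | c | p − c |

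The two costings differ by c. The 7-9% of invalid Pima readings cited in 6c i, each repeated once, raise the Pima term to 1.07p-1.09p in both rows and leave that difference at c.

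**Step 2: average over the rapid arm**

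Subjects with a prior count contribute nothing, so the overstatement per subject is s × c. The number of extra NHLS counts is 200 × s: 50 at s = 25% and 200 at s = 100%.

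**Step 3: per success**

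With C the mean rapid-arm cost excluding this test, (C + s × c)/0.70 − C/0.70 = s × c/0.70.

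| s (assumed) | Extra NHLS counts in 200 | Per subject | Per success |
|---|---|---|---|
| 25% | 50 | 0.25c | 0.36c |
| 50% | 100 | 0.50c | 0.71c |
| 75% | 150 | 0.75c | 1.07c |
| 100% | 200 | 1.00c | 1.43c |

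**Step 4: relative size**

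The proportional overstatement is s × (c/C), and the success proportion cancels. If one NHLS count were 0.5% to 5% of the mean 10-month cost, which is purely an assumption, the overstatement would be 0.5% to 5% at s = 100% and 0.25% to 2.5% at s = 50%. No rand amount can be derived from the protocol.

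**The case against.** The strongest reply is that nothing in the protocol calls this a study-only test. It stands under the rapid initiation procedures, and it has a consequence for care, because subjects whom Pima missed are recalled. Section 12a also says the study adds no samples or clinical procedures beyond routine care. On that reading the NHLS count is a back-up within the delivered strategy, and pricing every resource actually used is a legitimate trial-based method. Section 5a limits unit costs to resources serving patient care, and the exact base case could be left to a later analysis plan. Nothing is lost meanwhile, since tests are recorded by type.

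Much of this stands. Calling the test a study check is an inference, and the as-delivered cost deserves to be reported. But 11c does state a rule, and that rule prices everything. The wording in 5a does not clearly remove the test. For a subject already eligible on Pima, 6c i makes no action depend on the NHLS result. Section 12a also says the strategy only brings forward the timing of events, which does not describe a second count in one arm.

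A reader might go further in three ways that the protocol does not support:
- **Excluding the off-site third sputum sample (6c ii) as well.** It is for patients already diagnosed with TB, and culture is done only where needed. Standard-arm subjects also receive TB diagnosis (6d ii). Nothing shows that this sample is a study check or confined to one arm.
- **Removing successes that followed recall on an NHLS result.** That would reclassify outcomes in one arm on a post-randomisation event, against the intention-to-treat rule in 11a i and 11b. It would also break the Summary's definition of cost-effectiveness as cost per patient achieving the primary outcome.
- **Sizing the problem by number of tests.** Pima and NHLS tests need not cost the same, and subjects with a prior count are exempt.

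**Conclusion.** The point holds, and it is minor. Following 8e and 11c as written charges the rapid arm one extra NHLS CD4 count for each subject without a valid prior count, and nothing corresponding enters the standard arm. Relative to the strategy described in 5a, rapid-arm cost is overstated by s × c per subject and about s × c/0.70 per success, or 0.36c to 1.43c for s between 25% and 100%. This rests on the planned 70% success, an assumed range for s, an unknown c, and reading the exemption in 6c i as covering both CD4 tests.

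The direction is clear; materiality is not shown. Beside ten months of drugs, visits, staff and fixed costs, one CD4 count is probably small. It would be wrong to infer that the cost-effectiveness conclusion is unsafe, or that the test should not be done.

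**What to change.** In section 11c, state that rapid-arm cost per patient and cost per success will be reported in two ways: without the confirmatory NHLS CD4 count (the strategy as described in 5a) and with it (the strategy as delivered). Keep all subjects and all successes in their randomised arm in both. Also report the number of rapid subjects who started ART after recall on an NHLS result. The costing without the test still counts those subjects' successes, so this number shows how far it may flatter a strategy that relies on Pima alone. Leave the costing of the third sputum sample as it is. The testing and recall procedures themselves are not affected.

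The cost is a sentence or two in 11c and a second set of cost figures to present. No new data collection should be needed, because lab tests are already recorded by number and type (8e) and the Track 1 case report form captures the rapid-group tests (8c).

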#### *6c ii. TB test*

Sputum samples for patients with TB symptoms will immediately be sent to the on-site laboratory for testing using Xpert MTB/RIF. Each patient will be asked for two sputum samples to allow two Xpert tests to be run. Those with at least one positive Xpert test will be considered to have active TB. Those with two negative tests will be considered not to have TB. Those with inconclusive test results will be diagnosed clinically by the study nurse or the site doctor. Patients diagnosed with TB will be told of their results and escorted by the study assistant to the site's TB clinic, where TB treatment can be initiated.

A third sputum sample for all patients diagnosed with TB will be sent to the off-site National Health Laboratory Service laboratory for smear microscopy and culture if required. The NHLS lab results will be monitored by the study team. Any positive TB diagnosis not already made by the study nurse will be conveyed immediately to the site, and the patient will be contacted by the study assistant and asked to return to the clinic to initiate TB treatment.

The study site's standard procedures will be followed with regard to TB treatment. Under current South African guidelines, two weeks (14 days) of TB treatment is required prior to initiating ART for patients with a CD4 count  $\leq 350$  and eight weeks of TB treatment is required for patients with a CD4 count  $> 350$ . Study subjects diagnosed with TB and with CD4 counts  $\leq 350$  will be asked to return to the clinic between 14 and 28 days after study enrollment to continue with rapid ART initiation. Those returning in more than 28 days will be offered standard ART initiation. Subjects with TB and CD4 counts  $> 350$  will be advised to return for TB treatment only, then continue with standard ART initiation. Patients already on TB treatment but for less than 14 days at the time of study enrollment will also be asked to return once they have reached 14 days of TB treatment.

### *6c iii. Baseline lab tests, physical exam, and educational session*

Subjects who are eligible for ART will be enrolled in the study once treatment eligibility is confirmed. Using the same blood sample drawn earlier, the study nurse will perform the required baseline blood tests (creatinine, hemoglobin, ALT) and will perform a pregnancy test for female subjects in Track 1. (Track 1 rapid group subjects who are found to be pregnant will be transferred to Track 2 at this time.)

Subjects will then be examined by the study nurse, who will conduct the standard ART readiness physical examination. Either before or after the medical exam, depending on each day's patient flow, each subject will also meet individually or in a small group with the trained study assistant for an educational and counseling session on antiretroviral therapy, the importance of adherence and disclosure, and other actions to promote health while on ART. This will be a concise version of the education and counseling typically provided over the course of three visits under standard care. During this session, each subject will have an opportunity to ask questions and discuss concerns with the study assistant.

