#### *6d ii. Remaining ART readiness and initiation steps*

Subjects who are eligible for treatment will follow the site's standard procedures for initiating ART, based on South African guidelines. These include 1-3 return visits to the clinic for remaining laboratory tests (creatinine, full blood count, ALT, pregnancy, syphilis), TB diagnosis and treatment if required, adherence counseling, wellness education, and a physical exam. Medications will then be prescribed by the site doctor or primary health care nurse and dispensed by the site's pharmacy.

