## 10. Sample Size

Track 1: In a recent study we conducted in Johannesburg, we found that among patients eligible for ART, 46% initiated ART within 16 weeks of eligibility. In an analysis of data from the same Johannesburg site, we estimated that among more than 3000 patients initiated on ART in 2010 and 2011 who remained in care, 77% were virally suppressed at the routine 6-month viral load. We would thus expect approximately  $0.46 \times 0.77 = 35\%$  of those eligible to have both started treatment and be virally suppressed by the 6-month viral load. For our study site we conservatively estimate that 50% of those eligible for treatment in the standard group will be suppressed by 10 months after their HIV test. We anticipate that the rapid initiation strategy will increase the proportion suppressed to 70%.

For our primary analysis, using an  $\alpha$  of 0.05, power of 90%, 1:1 randomization, and an uncorrected Fisher's exact test, we would need to enroll 124 HIV positive ART-eligible subjects per group (248 total). We expect 70% of all HIV-positive patients to be eligible for ART under current South African guidelines on the day they test positive for HIV or make their first HIV care visit, based on results from published studies in South Africa. Therefore to reach 124 subjects per arm who are treatment eligible on the day of testing we will need to consent 177 subjects per group (354 total). To allow stratification in the analysis by sex and by site, we will consent up to 300 per group (600 total) to have adequate power. We will enroll in the study up to 67% of this total (enrollment=400).

The sample size for the Track 1 retrospective comparison group will be 120. This group will be limited to patients already found to be eligible for ART at one of the two study sites (Thuthukani). They will be compared with each of the two randomized prospective groups (rapid and standard). We expect that Thuthukani will account for approximately 60% of total prospective enrollment of 400, or 120 in each of the randomized prospective groups. We will thus aim to enroll the same the number of subjects into the retrospective comparison group as in each prospective group.

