#### 11b. Clinical outcomes analysis

For both tracks and for primary and secondary clinical outcomes, the analytic approach for clinical outcomes will be the same. All analyses will be by intention-to-treat: subjects will be analyzed according to the intervention they were supposed to receive, whether or not they adhere to the defined intervention.

The analysis will begin with a simple comparison of the two treatment groups with respect to baseline predictors of outcomes. We will then conduct a crude analysis comparing the proportion of patients achieving each dichotomous outcome by group and crude risk ratios and 95% confidence intervals

stratified by group. For average gestational age at ART initiation and average time on ART before delivery for Track 2, we will calculate the mean difference between groups and corresponding 95% confidence interval.

Since adherence has been a particular concern for pregnant women who were not eligible for ART under the previous guidelines, the primary outcome for Track 2 will be stratified in secondary analysis by CD4 count at the time of initial ANC visit if enrollment numbers by the end of the study period are large enough to allow a stratified analysis. Subjects in the prospective group found after ART initiation to have CD4 counts above 350 will be compared to those in the retrospective group who were offered AZT under the previous guidelines, while subjects in the prospective group found after ART initiation to have CD4 counts below 350 will be compared to those in the retrospective group who were offered full ART under the previous guidelines.

Because we will not be randomizing large numbers of patients in Track 1 and because no randomization will occur in Track 2, it is possible that some baseline covariates may be imbalanced by treatment arm. To adjust for potential differences by baseline covariates, a log-linear regression model will be used to estimate adjusted risk ratios and a linear regression will be used to adjust mean differences.

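### Women found pregnant after randomisation leave the rapid arm for Track 2, but the standard arm has no matching test timing or rule, so the pregnancy exclusion is applied unequally and conflicts with intention-to-treat

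*Protocol*

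**What the plan says.** Section 5c of the Protocol makes pregnancy an exclusion for Track 1, without distinction by arm. Sections 6b ii and 12e say that every criterion except treatment eligibility is settled before consent. Section 6b iv places randomisation straight after the questionnaire, before the CD4 count.

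In the rapid arm, Section 6c iii has the study nurse run the pregnancy test once eligibility is confirmed and the subject is enrolled. It then states: "Track 1 rapid group subjects who are found to be pregnant will be transferred to Track 2 at this time".

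In the standard arm, Section 6b iv ends personal contact with the study team after group assignment. Section 6b vi enrols these subjects on monitored CD4, TB and Stage 4/3 results and does not mention pregnancy. Section 6d ii lists the pregnancy test among the "remaining laboratory tests (creatinine, full blood count, ALT, pregnancy, syphilis") that the clinic does over one to three return visits. No section says what happens to a standard-arm woman who tests positive.

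Section 11b states: "All analyses will be by intention-to-treat: subjects will be analyzed according to the intervention they were supposed to receive". For Track 2, Section 5a states: "The study will not provide any direct clinical interventions for Track 2".

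**The concern.** A baseline exclusion confirmed after randomisation is harmless if both arms are tested at the same point and handled the same way. Here neither holds. Every eligible rapid-arm woman is due a test while she is with the study nurse, and a positive result moves her to another cohort. In the standard arm, testing depends on the woman coming back, and coming back is itself part of what the primary outcome measures. The two analysed groups would then differ in composition for a reason created by the allocation. That is the problem the intention-to-treat statement is meant to prevent.

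The primary Track 1 comparison is at stake. A lesser issue is the Track 2 prospective group, which would receive a few women who had already had study-delivered testing.

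**Working it through.** **Plan's own figure.** Section 10 uses an alpha "of 0.05, power of 90%, 1:1 randomization, and an uncorrected Fisher's exact test". It assumes that "50% of those eligible for treatment in the standard group will be suppressed by 10 months after their HIV test" and adds: "We anticipate that the rapid initiation strategy will increase the proportion suppressed to 70" per cent. The two-sided normal-approximation formula with pooled variance under the null and no continuity correction gives:

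n = [1.960 × √(2 × 0.6 × 0.4) + 1.2816 × √(0.5 × 0.5 + 0.7 × 0.3)]² / 0.2² = (1.358 + 0.869)² / 0.04 = 124 per group.

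This matches the statement that "we would need to enroll 124 HIV positive ART-eligible subjects per group (248 total"). The sample size is not in question. Planned enrolment is 400, or about 200 per arm.

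**Number removed.** The documents give neither the share of women nor the rate of unrecognised pregnancy. Assumptions: 50-60% women, 2-8% of them pregnant without knowing it. The affected share of an arm is q = 0.5 × 0.02 = 1.0% to 0.6 × 0.08 = 4.8%. From 200 rapid subjects that is 2.0 to 9.6. From the standard arm it is none, if no rule is applied there.

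**Shift in the primary difference.** Let p be the success rate in non-pregnant subjects and s the rate in pregnant women kept in the standard arm. With no true effect, the rapid arm shows p and the standard arm shows p(1 - q) + s × q. The spurious difference (rapid minus standard) is q(p - s). With p = 0.50:

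| s in retained women | q = 1.0% | q = 4.8% |
|---|---|---|
| 0% (all counted as failures) | +0.5 points | +2.4 points |
| 35% | +0.15 points | +0.7 points |
| 50% | 0 | 0 |
| 70% | -0.2 points | -1.0 points |

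The first row can occur because Section 11a i counts anyone without a six-month viral load within 10 months of enrolment as a failure, whatever the reason. The last row can occur because Section 7 describes immediate ART at the first antenatal visit for all pregnant women.

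**Error rates.** Taking q = 5%, just above the assumed range, 200 standard subjects are compared with 190 rapid subjects.

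- No true effect: the test rejects in 7.8% of trials if all retained women fail and in about 5.5% if 70% succeed, against a nominal 5%.
- 70% success in the rapid arm: power is 99.6% and 97.2% respectively, against 98.5% with no removals.
- At the minimum of 124 per arm, the corresponding power is 94.9% and 86.0%, against 90.0%.

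**Track 2.** Two to ten transfers are 2/153 = 1.3% to 10/153 = 6.5% of the planned prospective group, or 2/76 = 2.6% to 10/76 = 13.2% of the minimum group in Section 10.

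**The case against.** Four points can be made on the other side.

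- **Pregnancy was always an exclusion, and a general rule exists.** Section 8f iv says people found ineligible for any reason are not enrolled, and standard-arm enrolment waits for file review (Sections 6b vi and 8f ii). A pregnancy on file by then could be caught. This narrows the gap, so it cannot be assumed that every pregnant standard-arm woman stays in the denominator. It does not close the gap: the rule acts before enrolment, sets no pregnancy test for the standard arm, and leaves out women tested later or never.
- **Transfer is not stated to mean removal from analysis.** Section 6c iii does not say that these women leave the Track 1 analysis. That is the natural reading, however. Section 6c v expressly keeps rapid subjects who return late in their group for analysis, and Section 6c iii has no such clause.
- **The direction is not fixed.** A reader might infer that the standard arm, by keeping women who start ART quickly through antenatal care, biases the result toward no difference. The documents do not support that. The failure rule in Section 11a i can push the result the other way, and late or absent testing weakens the antenatal route.
- **Track 2 is hardly contaminated.** A reader might infer that it fills with study-managed women. Section 6c iii places the transfer before the physical examination and education session, and so before the prescription in Section 6c iv. Pregnant women at the site already belong to the Track 2 population (Section 5c). What remains is a small inconsistency with Section 5a, because these women have had study CD4 testing, TB symptom screening and baseline blood tests.

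**Conclusion.** The concern holds as a conflict within the Protocol. Sections 5c, 6c iii, 6d ii and 11b cannot all be followed as written without unequal post-randomisation exclusion.

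Under the stated assumptions, about 2 to 10 of 200 rapid subjects and no standard subjects would be removed, shifting the primary difference by roughly -1 to +2.4 points. The sign depends on whether pregnant women retained in the standard arm have a six-month viral load within 10 months. The frequency of unrecognised pregnancy is an assumption throughout; the documents give no figure. The upper ends also assume that no standard-arm pregnancies are caught before enrolment.

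Against a planned 20-point effect this is small, and power at 200 per arm stays above 97%. The stronger conclusions that the bias has a known direction, that it threatens the trial's main result, or that Track 2 is materially contaminated are not supported. The flaw should be corrected because it affects the integrity of the randomised comparison and is cheap to remove.

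**What to change.** Reconcile Sections 5c, 6c iii, 6d ii and 11b so that both arms are handled alike, by one of two routes.

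1. **Keep them in the analysis.** State that women found pregnant after randomisation, in either arm, stay in their randomised Track 1 group for the primary analysis and are not counted in the Track 2 comparison, with their care following site guidelines. The cost is a few pregnant women in Track 1, and a matching line where Sections 4a and 5c define that population as non-pregnant.
2. **Exclude before allocation.** Apply the pregnancy exclusion to all women, by the same method, before the randomisation envelope is opened. The cost is more point-of-care pregnancy tests, since they extend to all consented women and not only those found eligible for ART. At 50-60% women, that is 300 to 360 of the 600 consented, compared with 200 to 240 of the 400 enrolled. Losing subjects this way is affordable: if even 6% were excluded from each arm, 188 of 200 would remain, with power of 97.9%.

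Either route removes the asymmetry. Neither changes the sample size.
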